**Titrating correctional insulin in the POC-arm and CGM-arm**			
Titration of sliding scale insulin is done based on the decision of whether the patient is insulin resistant (add insulin) or insulin sensitive (subtract insulin) by adjusting levels of Recommended insulin (U) by the column Insulin change (U). The trend in increasing or decreasing basal and/or prandial insulin might guide this decision.			

For CGM-arm patients, real-time hypo- and hyperglycaemic audible CGM alarms are turned on in the in-hospital diabetes teams’ nurse stations on tablets. When the in-hospital diabetes teams are on ward rounds, they are equipped with a smartphone with the same alarm setup as the tablets. Hypoglycaemic alarms occur when glucose levels are <3.9 mmol/l [<70 mg/dl]. POC glucose testing must confirm hypoglycaemia on CGM due to reduced CGM sensor accuracy during hypoglycaemia [19]. Hyperglycaemic alarms occur when glucose levels are >13.9 mmol/l [>250 mg/dl] for two hours to avoid alarm fatigue. To avoid insulin stacking, hyperglycaemia on CGM is only corrected by warning of hyperglycaemic alarms and not by random viewing of CGM glucose levels. For POC-arm patients, hypo- and hyperglycaemia detected by POC glucose testing are corrected when observed.

POC-arm and CGM-arm patients are peroperatively monitored by POC glucose testing only. During fasting perioperatively (or insufficient food intake), patients are managed by glucose-insulin-potassium infusion [38]. When the patient eats a full meal again, insulin regimens are resumed.

From approx. 15:00 h to 08:00 h, and at weekends, the in-hospital diabetes teams are unavailable, and diabetes management is performed by ward nurses by POC glucose testing only in both arms.

### Titrating basal, prandial, and correctional insulin

Basal, prandial, and correctional insulin are titrated daily by the in-hospital diabetes teams in the POC-arm and CGM-arm. Titration is done by operational algorithms (Table 1) from 24-hour retrospective CGM data or POC glucose levels.

The three rules below apply for titrating basal and prandial insulin in both arms, aiming for glucose levels of 5.6–7.8 mmol/l [100–140 mg/dl]:*Rule of the lowest*: If glucose levels both *below and above* the range of 5.6–7.8 mmol/l [100 – 140 mg/dl] in Table 1 are observed during a titration period (and for CGM-arm patients above the listed percentage thresholds for decreasing or increasing basal insulin in Table 1, respectively), the lower glucose levels and hereby lowering of basal and/or prandial insulin must be prioritised.*Rule of the extremes*: The extremes of glucose levels *all below* or *all above* or *within and above* or *within and below* the range of 5.6–7.8 mmol/l [100–140 mg/dl] are prioritised in Table 1. For example, for CGM-arm patients, if ≥5% of glucose levels are <3.0 mmol/l [<54 mg/dl] and ≥5% of glucose levels are in the range of 3.0–3.8 mmol/l [54–69 mg/dl] during a titration period, the Table 1 recommendations for ≥5% of glucose levels <3.0 mmol/l [<54 mg/dl] (i.e., the “extreme” furthest away from the range of 5.6–7.8 mmol/l [100–140 mg/dl]) are followed.*Rule of missingness*: If all CGM data are temporarily missing (e.g., due to missing signal between the smartphone and CGM) or of unusable quality (e.g., due to multiple pressure-induced sensor attenuations), titration of insulin in CGM-arm patients is guided by POC glucose levels.

### Primary outcome

We assess the difference between arms regarding time in range (TIR), i.e., percentage of time during admission with glucose levels of 3.9–10.0 mmol/l [70–180 mg/dl] [37].

### Secondary outcomes

#### Glycaemic outcomes

Outcomes will be reported according to the newest CGM consensus [39]. Outcomes include (mmol/l) [mg/dl]: TIR per day 3.9–10.0 [70–180], time above ranges (TAR) >10.0 [>180], TAR >13.9 [>250], time below range (TBR) <3.9 [<70], TBR <3.0 [<54], and mean glucose levels. Glycaemic variability is reported as the CGM glucose distribution's standard deviation (SD) and coefficient of variation (CV). We report events, i.e. three consecutive CGM glucose levels, of hypoglycaemia <3.9 [<70], hypoglycaemia (level 1) 3.0–3.8 [54–69], hypoglycaemia (level 2) < 3.0 [<54], and the number of reoccurring hypoglycaemic events after the first episode of hypoglycaemia.

#### Clinical outcomes

We assess the length of hospital stay, any in-hospital related complications occurring at least one day after randomisation (e.g. acute kidney injury, death during hospitalisation, transfer to intensive care unit, etc.), the number of times basal, prandial, and correctional insulin is given in total *and* correctly given (according to Table 1 specifications), daily insulin doses, and readmission and death 30 days after hospitalisation.

### Tertiary outcomes

We assess the level of satisfaction with in-hospital CGM among the in-hospital diabetes teams and patients by questionnaires. Exploratory, we will identify which patients benefit from the in-hospital CGM setup (Fig. 2) in regard to glycaemic outcomes. We also evaluate how often the titration algorithm (Table 1) is followed correctly or not for both basal, prandial, and correctional insulin in both arms. The effects of the in-hospital diabetes teams are evaluated by comparing outcomes between periods when the in-hospital diabetes team are at work and off shifts.

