## Abstract

**Background:**

Worldwide, up to 20 % of hospitalised patients have diabetes mellitus. In-hospital dysglycaemia increases patient mortality, morbidity, and length of hospital stay. Improved in-hospital diabetes management strategies are needed. The DIATEC trial investigates the effects of an in-hospital diabetes team and operational insulin titration algorithms based on either continuous glucose monitoring (CGM) data or standard point-of-care (POC) glucose testing.

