**Discussion:**

The DIATEC trial will show the glycaemic and clinical effects of in-hospital CGM handled by in-hospital diabetes teams with access to operational insulin titration algorithms in non-critically ill patients with type 2 diabetes. The DIATEC trial seeks to identify which hospitalised patients will benefit from CGM and in-hospital diabetes teams compared to POC glucose testing. This is essential information to optimise the use of healthcare resources before broadly implementing in-hospital CGM and diabetes teams.

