### Trial design and population

The DIATEC trial is a two-armed, two-site, prospective, randomised, open-label, blinded-endpoint (PROBE) trial (Fig. 1). In both arms (a POC-arm and a CGM-arm), hospitalised patients are monitored by POC glucose testing five times daily. Diabetes management is done by ward nurses guided by in-hospital diabetes teams. The in-hospital diabetes teams have operational algorithms for the titration of basal, prandial, and correctional insulin in both arms. In the POC-arm, insulin titration is guided by only POC glucose measurements. In the CGM-arm, insulin titration is guided by CGM data only, accessed by the in-hospital diabetes teams.

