**Insulin orders during admission**			
**Basal insulin** *(mandatory order)*			
Basal insulin is given at lunch to allow same-day insulin titration decisions during the morning to take effect. Starting basal insulin dose is 0.25 U/kg, rounded to the nearest unit. Exceptions are:			
• Basal insulin dose is 0.20 U/kg in patients aged >75 years and/or with an eGFR ≤60 ml/min/1.73 m^2^ and/or body mass index (BMI) ≤ 22.5.			
• Basal insulin is continued on the usual out-hospital dose in patients treated with basal insulin at home.			
• In perioperative or fasting patients, basal insulin is paused on the day of surgery or during fasting and patients are managed by glucose-insulin-potassium (GIK) infusion. If the postoperative patient eats a full meal before 22:00 h, GIK infusion is stopped and half basal insulin dose is given. The full basal insulin dose is continued the following days.			
**Prandial insulin** *(ordered at the discretion of the in-hospital diabetes teams when glucose levels >10.0 mmol/l [>180 mg/dl] are observed postprandially for 1-2 days)*			
Starting total prandial insulin dose is 0.25 U/kg, rounded to the nearest unit, and given in three equally divided doses for breakfast, lunch, and dinner. Exceptions are:			
• Prandial insulin dose is 0.20 U/kg in patients aged >75 years and/or with an eGFR ≤60 mL/min/1.73 m^2^ and/or body mass index (BMI) ≤22.5.			
• Prandial insulin is continued on the usual out-hospital dose in patients treated with prandial insulin at home.			
• In perioperative or fasting patients, prandial insulin is paused on the day of surgery or during fasting.			
**Correctional insulin** *(mandatory order)*			
Glucose Level		Recommended insulin (U)	Insulin change (U)
mmol/l	mg/dl		
< 10.0	< 180	0	0
10.0 – 11.9	180 – 214	4	± 2
12.0 – 15.9	215 – 286	6	± 3
16.0 – 19.9	287 – 358	8	± 4
≥ 20.0	> 358	10	± 6

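### The on-shift versus off-shift comparison cannot be read as the effect of the diabetes team: it is not randomised, it compares different clock hours, and team-set doses carry over

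*Protocol article*

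**What the plan says.** Tertiary outcomes in the protocol article states that the effects of the teams are "evaluated by comparing outcomes between periods when the in-hospital diabetes team are at work and off shifts". Statistical considerations brings the same contrast back in the per-protocol analysis of glycaemic outcomes, where on-shift CGM data are set against data from when the team is away.

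The shift is defined in the text that follows the Table 1 rows on correctional insulin: "From approx. 15:00 h to 08:00 h, and at weekends, the in-hospital diabetes teams are unavailable". In those hours "diabetes management is performed by ward nurses by POC glucose testing only in both arms".

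Trial design and population says of both arms: "Diabetes management is done by ward nurses guided by in-hospital diabetes teams". The arms differ in whether the team sees CGM data, not in whether there is a team.

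The abstract's Background says the trial "investigates the effects of an in-hospital diabetes team and operational insulin titration algorithms"; the sentence goes on to name CGM and POC data as the two bases for titration. The abstract's Discussion says the trial seeks to identify "which hospitalised patients will benefit from CGM and in-hospital diabetes teams compared to POC glucose testing". The closing Discussion repeats the aim of finding who benefits from CGM and a team.

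**The concern.** The sentence in Tertiary outcomes is causal and names its contrast, so it fixes how a result will be read. Three features stand in the way of that reading.

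- No arm lacks the team, so the contrast is observational even though it sits inside a randomised trial.
- On-shift and off-shift hours fall at different times of day. In-hospital diabetes management itself treats night as fasting and day as non-fasting, and ties a different insulin component to each.
- Decisions taken on shift keep acting off shift, so the comparator is not free of the team.

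Followed as written, the analysis could report a team effect where there is none, or understate a real one. The abstract and the closing Discussion add to the risk by naming the team as part of what is being tested against POC glucose testing.

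**Working it through.** **1. Is there a plan figure to reproduce?** None is given for the shift comparison. Its only numbers used below are N = 166, SD 23 and the 10-point difference from the sample-size section. They agree with each other: 2 × (1.960 + 0.842)² × 23² / 10² ≈ 83 per arm, or 166.

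**2. Weekly hours, from the stated shift times (approximate in the article, taken here as exact).**
- On shift: 5 days × 7 h = 35 h, or 35/168 = 20.8%.
- Off shift: 168 − 35 = 133 h, made up of:
  - 15:00–24:00 on seven days: 63 h (47.4%)
  - 00:00–08:00 on seven days: 56 h (42.1%)
  - weekend 08:00–15:00: 14 h (10.5%)
- All weekend hours together: 48 h (36.1% of off-shift time).
- Off-shift hours with no on-shift counterpart on the clock: 63 + 56 = 119 h (89.5%).

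**3. Difference produced by clock time alone.** Let TIR be A at 08:00–15:00 on any day and B at other hours, with no team effect, D = A − B, and patient time spread evenly over the week.

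On minus off = A − (14A + 119B)/133 = (119/133) × D = 0.895 × D.

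For a patient with no weekend hours the factor is 1. The article gives no D, so a range is shown:

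| Assumed D (points) | Spurious difference (points) |
|---|---|
| 2 | 1.8 |
| 5 | 4.5 |
| 10 | 8.9 |
| 15 | 13.4 |

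**4. The sign depends on the profile.** Assumed TIR for 08–15 h / 15–24 h / 00–08 h, zero team effect:
- 50/60/80: off = (14×50 + 63×60 + 56×80)/133 = 67.4; difference −17.4.
- 60/60/70: off = (14×60 + 63×60 + 56×70)/133 = 64.2; difference −4.2.
- 70/60/60: off = (14×70 + 63×60 + 56×60)/133 = 61.1; difference +8.9.

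**5. Chance of a false significant result.** Assume 166 patients with data in both periods, SD 23 in each, and within-patient correlation ρ from 0.3 to 0.7. SE = 23 × √(2(1 − ρ)) / √166, which runs from 2.11 (ρ = 0.3) to 1.38 (ρ = 0.7). At two-sided 5%, with no team effect, the chance is 14–25% for D = 2, 56–90% for D = 5, and about 99% or more for D = 10. The SD of 23 is the planning value for a whole admission; a larger SD for part-day TIR would lower these chances.

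**6. Carry-over.** Table 1 says: "Basal insulin is given at lunch to allow same-day insulin titration decisions during the morning to take effect". The basal dose is judged on glucose between midnight and breakfast, which is wholly or mostly off shift. From Monday to Thursday, 17 of the 24 hours after a lunch dose (15:00 to 08:00) are off shift. Team-set dinner doses and correction scales also apply in the evening. If a share c of a true effect persists off shift, the contrast shows only (1 − c) of it.

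**7. Is there a remedy in the text?** Statistical considerations describes a day/night split, but for comparisons between arms. A between-arm comparison by shift would inform on CGM access while a team is present, not on the team.

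**The case against.** The strongest reply is that this is one sentence on a tertiary outcome in an article summarising a longer plan, which may hold clock-time matching or adjustment. That is fair as to missing detail, and the absence of a model is not the complaint. The complaint is the stated reading of a stated contrast, which the article makes itself.

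Several stronger readings are tempting but unsupported:

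- *A useful team will look harmful.* This needs TIR to be lower by day than by night. The article gives no TIR by clock time, and the profiles in step 4 give either sign.
- *All of the team's benefit is credited to off-shift time.* The team also titrates prandial and correctional insulin and, in the CGM-arm, receives real-time alarms, so part of its effect can fall within the shift. No text ranks the lunchtime basal dose as its main action.
- *The shift comparison will drive resource advice.* The resource statements are tied to identifying which patients benefit, a separate exploratory aim.
- *The abstract hides the design.* Its Methods paragraph says both arms are team-guided, and its Discussion says the trial seeks to identify, not that it will show, who benefits. The phrase setting CGM and teams against POC testing is still loose, because the POC-arm has the team too.

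It is also true that weekends supply some off-shift hours at matching clock times. But they are 14 of 133, and the article does not restrict the comparison to them.

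**Conclusion.** The concern holds for the interpretation of a tertiary analysis. As described, the on/off-shift contrast cannot identify the team's effect: it is not randomised, 89.5% of off-shift hours have no on-shift counterpart on the clock, and team-set doses act into the comparator period. These statements rest on the article alone.

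The size rests on assumptions. Clock time alone produces about 0.9 × D, and a gap of only 5 points would give a false significant result more often than not under the SD and correlations in step 5. The direction is unknown. The 10 points used for sample size refer to the difference between arms, so they give only a rough sense of scale.

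A reader should not infer that the primary TIR comparison is affected. It compares randomised arms over the whole admission.

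**What to change.** 1. In Tertiary outcomes and Statistical considerations, report on-shift and off-shift outcomes descriptively and do not attribute the difference to the team.
2. If an exploratory analysis is wanted, compare 08:00–15:00 on weekdays with 08:00–15:00 at weekends within patient, in a mixed model with a patient random effect and day of stay. State that weekend hours still run on doses the team set during the week and that ward conditions may differ at weekends. This matches the clock; it does not isolate the team.
3. Reconcile the statement that the teams titrate insulin daily with the statement that they are unavailable at weekends, because this decides what a weekend hour represents.
4. Reword the abstract's Background and Discussion and the closing Discussion so that the randomised claim is CGM-guided versus POC-guided titration with a diabetes team in both arms.

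The cost is analysis and wording, with no new data. The matched analysis uses fewer hours (35 on-shift against 14 off-shift per week). Entry requires an expected stay of only two days after enrolment, so some patients will have no weekend day and will contribute little.

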### Data collection and trial procedures

A flowchart of trial procedures is provided in the Supplementary Table.

### Glucose data

Glucose data are collected by the CE-marked CGM Dexcom G6 (Dexcom Inc., San Diego, USA). The accuracy of in-hospital CGM use has been verified in previous studies [20].

### Demographic- and clinical data

The following data are recorded: Date of birth, ethnic origin, gender, height, and body weight at the time of admission. Blood pressure, pulse, oxygen saturation, and respiratory rate will be used to assess the National Early Warning Score [40] at inclusion.

### Medical history, medications, and concomitant disease

Information from patients’ electronic health records regarding co-morbidities, medical history, and intercurrent disease is registered at baseline and throughout the course of the trial.

### Laboratory tests

Blood samples upon inclusion include haemoglobin A1c, admission glucose, estimated glomerular filtration rate, and daily C-reactive protein measurements.

### Questionaries

Questionaries about the patient’s experiences with having their diabetes managed by in-hospital diabetes teams and if the CGM has been troublesome in any way are developed from The Diabetes Treatment Satisfaction Questionnaire for Inpatients [41]. Questionnaires for the in-hospital diabetes team members on whether CGM is an advantage or not compared to POC glucose testing in managing in-hospital diabetes patients have been developed from previously used questionaries [15].

### Statistical considerations

Glycaemic outcomes are compared between arms for daytime and nighttime and the total day. Continuous variables are compared between arms by linear regression analysis. A zero-adjusted Gamma distribution accommodates the positivity and exact zero in the outcomes. Categorical variables are compared with the chi-squared test. Discrete variables are compared with Poisson regression or negative binomial regression. A linear mixed model is applied for repeated measures of daily insulin dose and C-reactive protein levels. In addition, a per-protocol analysis will be performed for glycaemic outcomes, including only CGM data from when the in-hospital diabetes teams are on shifts (and compared to when the in-hospital teams are not on shifts) and where expert decisions and appropriate actions on titrating insulin, according to Table 1 and correcting hypo- and hyperglycaemia are made. Missing data is handled by multiple imputation methods. Statistical significance is set at a two-sided *P*-value ≤0.05.

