### The sample size for the primary outcome

From our own studies on patients with diabetes admitted with pneumonia at NOH, we know that the mean TIR (±SD) is approximately 60–70%±20–25%  [10, 15]. A recent in-hospital CGM trial found a TIR (±SD) of 50%±25% [23]. If the expected difference between arms on TIR is set at 10 percentage points, SD to 23%, statistical power to 80%, and an alfa level of 5%, the inclusion of 166 patients is required. With a dropout rate of 20%, we aim to include 208 patients.

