### Randomisation

Randomisation is performed in the eCRF by a blocked randomisation list to ensure equal distribution of patients between the sites NOH and HGH and between arms. The randomisation list was set up by independent personnel not involved in other parts of the trial.

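### The stated comparison of time in range names no term for site or baseline glycaemia, so precision obtainable from data already collected may be forgone; the planned 80% power is not affected

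*Protocol article*

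**What the plan says.** The Statistical considerations section of the protocol article assigns a method to each type of outcome. For continuous outcomes it reads: "Continuous variables are compared between arms by linear regression analysis". No site term and no baseline variable is mentioned, and TIR has no separate model of its own. The next sentence adds: "A zero-adjusted Gamma distribution accommodates the positivity and exact zero in the outcomes". It does not say whether TIR is one of those outcomes; linear regression is the natural reading for TIR.

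Three other sections bear on the point:

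- Randomisation describes "a blocked randomisation list to ensure equal distribution of patients between the sites NOH and HGH and between arms".
- Laboratory tests states: "Blood samples upon inclusion include haemoglobin A1c, admission glucose, estimated glomerular filtration rate".
- The sample size section says the "expected difference between arms on TIR is set at 10 percentage points" and uses an SD of 23%, 80% power and a 5% alpha. It arrives at 166 patients, or 208 allowing for 20% dropout. The SD is not reduced for covariates.

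**The concern.** When randomisation is balanced within site, differences between sites cannot contribute to the difference between arms. A model without site still counts that variation in the residual, so the standard error is too large whenever the sites differ. Likewise, any variation in TIR that HbA1c and admission glucose predict stays in the residual if they are not used. The article describes no TIR value before randomisation, so these two measurements are the obvious baseline covariates.

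At stake are the width of the confidence interval for the primary result and protection against chance imbalance in baseline glycaemia. The design has little margin. The article itself cites SDs of 20–25% and of 25%, so the planning value of 23% is not at the upper end. The trial is also open-label, and a covariate set chosen after results by arm are known is hard to defend.

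**Working it through.** **Inputs from the article.** Difference 10 points, SD 23, two-sided alpha 5%, power 80%, 166 evaluable patients. Equal allocation (83 per arm) is assumed.

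**Reproducing the plan.** By the normal approximation, n per arm = 2 × (1.960 + 0.842)² × 23² / 10² ≈ 83.04, about 166.1 in total. Strict rounding up gives 84 per arm (168), within 2 of the stated 166. Dropout: 166 / 0.8 = 207.5, hence 208. With 83 per arm, SE = 23 × √(2/83) = 3.57 and power = Φ(10/3.57 − 1.96) = 80.0% (79.5% by the t-test). The stated figures therefore need no adjustment to hold.

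**Effect of covariates.** Let R² be the share of TIR variance explained by site, HbA1c and admission glucose together. The article gives no value, so a range is assumed. Residual SD = 23 × √(1 − R²); 95% CI half-width = 1.96 × residual SD × √(2/83).

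| Assumed R² | Residual SD | CI half-width (points) | Power at 166 | Total N for 80% power |
|---|---|---|---|---|
| 0 | 23.0 | 7.0 | 80.0% | 168 |
| 0.05 | 22.4 | 6.8 | 82.0% | 158 |
| 0.10 | 21.8 | 6.6 | 84.0% | 150 |
| 0.20 | 20.6 | 6.3 | 87.9% | 134 |
| 0.30 | 19.2 | 5.9 | 91.7% | 118 |

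**Effect of site alone.** Assume two equal sites whose mean TIR differs by D, with arms balanced within site. Then R² = (D/2)² / 23², and the residual SD s = √(23² − D²/4). With site omitted, the actual two-sided error rate is 2 × [1 − Φ(1.96 × 23 / s)].

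| Assumed D (points) | R² | Actual alpha, site omitted | Power, site omitted | Power, site included |
|---|---|---|---|---|
| 5 | 0.012 | 4.9% | 80.1% | 80.4% |
| 10 | 0.047 | 4.5% | 80.6% | 81.8% |
| 15 | 0.106 | 3.8% | 81.3% | 84.2% |

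**If the SD is larger than planned.** At SD 25, unadjusted power with 83 per arm is 73.1%. An R² of 0.15 would bring the residual SD back to 25 × √0.85 ≈ 23.0, and power to about 80%.

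**The case against.** The strongest objection is that the article is silent rather than wrong. A reader might infer that the primary comparison is fixed as an unadjusted regression. The text does not say so: linear regression can carry covariates, the word unadjusted does not appear, and the article is a summary of a fuller plan that may list them. This stands, and it limits the point to what follows if the published wording is applied as it is.

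A reader might also infer that the trial is underpowered or gives away power it relied on. The documents do not support that either, since the stated 80% reproduces without any adjustment at SD 23.

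Three further reservations hold. The article reports no association between HbA1c or admission glucose and TIR, and no difference in TIR between the sites, so every gain above depends on an assumption. The Randomisation section does not use the word stratified; balance of arms within each site is a reasonable reading, not a stated fact. And leaving site out, on that reading, errs on the conservative side, so the type I error is protected.

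What remains is that the article gives a method for each outcome type and mentions neither site nor baseline glycaemia, although the design and the data collection make both available.

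**Conclusion.** The point holds as one of forgone precision, not as an error in the sample size or a threat to validity. With an assumed R² of 0.05 to 0.30, adjustment would lift power at 166 evaluable patients from about 80% to about 82–92%. Most of that would have to come from baseline glycaemia, since site alone is worth only about 0.3 to 3 points for site differences of 5 to 15 points. Omitting site would put the actual error rate at about 4.9% to 3.8% instead of 5%. The site figures rest on equal-sized sites and balance within site. If the covariates turned out to predict little, the gain would be small, but so would the cost: three extra terms reduce the residual degrees of freedom from 164 to 161.

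**What to change.** Before unblinding, specify the primary model as TIR = arm + site + HbA1c + admission glucose, with both laboratory values being those taken at inclusion. Report the adjusted mean difference between arms in percentage points with a 95% CI, and keep the unadjusted comparison as a sensitivity analysis.

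This costs one sentence in the analysis plan. It needs no new data and no change to the sample size. If the analysis plan already specifies this model, no change is needed.

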**Titrating basal, prandial, and correctional insulin**			
**Titrating basal and prandial insulin in the POC-arm**			
Titration of basal insulin (mmol/l) [mg/dl] is done daily by POC glucose levels during the night from 00:00 h till breakfast and is done prior to administration at lunch. Titration of prandial insulin for a specific meal is done by the pre-prandial POC glucose levels of the subsequent meal and for dinner, the POC glucose level before bedtime (22:00 h):			
• < 3.0 [< 54]: Decrease insulin dose by 30%.			
• 3.0 – 3.8 [54 – 69]: Decrease insulin dose by 20%.			
• 3.9 – 5.5 [70 – 99]: Decrease insulin dose by 10%.			
• 5.6 – 7.8 [100 – 140]: No changes.			
• 7.9 – 10.0 [141 – 180]: Increase insulin dose by 10% if no hypoglycaemic events are observed the previous day.			
• 10.1 – 15.0 [181 – 270]: Increase insulin dose by 20% if no hypoglycaemic events were observed the previous day.			
• >15.0 [>270]: Increase insulin dose by 30% if no hypoglycaemic events were observed the previous day.			

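### The mixed model for daily insulin dose and CRP names no starting value, which costs precision (not validity) because the starting dose is set by the patient and not by the arm

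*Protocol article*

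**What the plan says.** Under Clinical outcomes, the secondary outcomes include "daily insulin doses". Statistical considerations gives the analysis: "A linear mixed model is applied for repeated measures of daily insulin dose and C-reactive protein levels". No starting-value covariate, time term, arm-by-time term or measurement scale is stated. Two more general sentences stand in the same paragraph: "Continuous variables are compared between arms by linear regression analysis" and "A zero-adjusted Gamma distribution accommodates the positivity and exact zero in the outcomes". Neither says whether it applies to insulin dose or CRP.

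Table 1 describes how a dose arises. For patients without home insulin: "Starting basal insulin dose is 0.25 U/kg, rounded to the nearest unit", with a reduced rate of 0.20 U/kg for older patients, reduced eGFR or low BMI. For the others: "Basal insulin is continued on the usual out-hospital dose in patients treated with basal insulin at home". Prandial insulin follows parallel rules. Basal and prandial doses are then titrated daily in steps of 10, 20 or 30%, for example "Increase insulin dose by 20% if no hypoglycaemic events were observed the previous day". Correctional insulin follows a different logic: fixed units by glucose band, changed by a fixed number of units.

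Laboratory tests lists "daily C-reactive protein measurements". CRP does not appear under the primary, secondary or tertiary outcomes.

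**The concern.** Daily insulin dose is the most direct record of what the two titration algorithms did, and it will be needed to explain any difference, or lack of one, in time in range. On any given day a patient's basal or prandial dose is mainly the starting dose carried forward. Weight, age, eGFR, BMI and home treatment set that start, and the arm does not. If the arm main effect is tested without it, the spread in starting doses stays in the between-patient variance against which the arms are compared. A real difference in titration may then go undetected, although information already in the record would have removed much of that variance. The same holds for CRP to the extent that the inclusion value predicts later values.

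**Working it through.** **The plan's own figure.** The only power statement is for time in range: difference 10 points, SD 23, power 80%, two-sided 5%. Per arm, n = 2 × (1.960 + 0.842)² × 23² / 10² = 83.04, about 166 in total, and 166 / 0.8 = 207.5, so 208. Both stated figures reproduce. Nothing is stated for insulin dose or CRP; 83 per arm is carried forward as the evaluable number.

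**Step 1: general size of the loss.** Let ρ be the correlation between the starting value and the later mean. Adjustment multiplies the residual variance by 1 − ρ². Choose an effect that gives 80% power with the starting value in the model (standardised effect 10/23 = 0.435). Without it, power is Φ(0.435 × √(1 − ρ²) × √(83/2) − 1.96).

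| ρ | 1 − ρ² | Power without starting value |
|---|---|---|
| 0.3 | 0.91 | 76% |
| 0.5 | 0.75 | 68% |
| 0.7 | 0.51 | 52% |
| 0.8 | 0.36 | 39% |
| 0.9 | 0.19 | 23% |
| 0.95 | 0.098 | 14% |

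More than half of the 80% is lost only from ρ of about 0.8 upward. The table serves CRP too, at whatever correlation applies; the documents give none.

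**Step 2: simulation of the dosing rules.** From the article: 0.20 or 0.25 U/kg or home dose, multiplicative daily movement, correctional insulin added in units. Assumed, because the article gives no figures: weight 88 kg (SD 20); half at each rate; home dose median 30 U, with CV 0.5 at 30% home users and 0.6 at 50%; 2, 4 or 6 days; a 15% dose difference reached on the last day. Steadier titration has patient-slope SD 0.05 and daily SD 0.08 on the log scale, with a mean of 2 correctional units. Noisier titration has 0.10, 0.12 and 6 units. Patient means over the days after the start stand in for the arm main effect of a balanced random-intercept mixed model. There were 400 runs per setting, so the Monte Carlo standard error is at most 2.5 points.

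| Home users | Days | Titration | ρ | Units, no start | Units, with start | Log, with log start | Slope in units, incl. starting day |
|---|---|---|---|---|---|---|---|
| 50% | 2 | noisier | 0.92 | 16% | 78% | 86% | 73% |
| 30% | 2 | steadier | 0.96 | 26% | 100% | 100% | 100% |
| 30% | 2 | noisier | 0.89 | 23% | 83% | 88% | 80% |
| 30% | 4 | steadier | 0.92 | 16% | 85% | 91% | 78% |
| 30% | 4 | noisier | 0.81 | 18% | 36% | 42% | 33% |
| 30% | 6 | noisier | 0.69 | 11% | 15% | 22% | 14% |
| 0% | 4 | steadier | 0.80 | 49% | 91% | 91% | 89% |
| 0% | 4 | noisier | 0.59 | 30% | 42% | 42% | 42% |
| 0% | 6 | noisier | 0.47 | 16% | 21% | 23% | 20% |

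Across all 27 settings run (including a third level with 15 correctional units), the starting dose raised power every time. Three things follow:

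- Most of the gain comes from the starting dose. The log scale adds about 0 to 14 points beyond it.
- A slope contrast that includes the starting day recovers much of the loss without a covariate.
- In long, noisy stays power is low either way, and the gain can be as small as about 4 points.

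**The case against.** The strongest reply is that the article does not say what a critic might read into it. A reader might infer that doses are compared in raw units. The text is silent on scale, and a model for log dose is still a linear mixed model. A reader might also infer that the starting value has been excluded. A journal summary commonly leaves covariates, time terms and contrasts for one secondary outcome to the full plan, so silence is not exclusion. Both replies stand, and this point is therefore a recommendation on precision, not a charge of error.

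A third inference would be that the plan throws away most of its power. The documents do not support that. They give no dose SD, correlation, home-insulin share, length of stay or expected dose effect, and the loss ranges from a few points to most of the power depending on those inputs. It also presumes a test of the arm main effect. If the planned contrast is arm by time with the starting day among the repeated measures, the random patient effect already absorbs much of the spread.

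Finally, the percentage-step argument reaches neither correctional insulin, which moves in units, nor CRP, so it cannot justify a log scale for everything. Randomisation protects against bias, and the primary outcome is untouched.

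What remains is that the stated model names no starting value, that the dosing rules make it strongly predictive, and that it can be had at almost no cost.

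**Conclusion.** The point holds as a matter of precision for a secondary outcome and for CRP. As written, the mixed model names no starting value, while the protocol's own rules make the starting dose a major determinant of later basal and prandial doses, independent of arm. If the arm main effect is tested without it, the assumed inputs give these losses:

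- **No home users, noisier titration, four days:** about 10 points (42% down to 30%).
- **Many home users, two-day stays:** well over half of the power (for example 78% down to 16%).

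The loss is smaller with an arm-by-time contrast that includes the starting day. All these figures rest on assumed distributions and on a balanced approximation to the mixed model. They show direction and range, not the loss this trial will have. The comparison stays unbiased, and time in range and its sample size are unaffected.

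The absence of CRP from the outcome lists is a separate, minor labelling matter: its daily collection and its analysis are both disclosed, but its status is not.

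**What to change.** In Statistical considerations, or in the full analysis plan if it does not already say so:

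1. **Insulin dose.** Add the starting dose as a covariate in the mixed model. Define it as the home dose, or otherwise the dose given by the Table 1 rule. Both follow from pre-randomisation data, so neither can be influenced by the arm, unlike a dose first ordered after randomisation. State whether the arm effect is a main effect or an arm-by-time contrast.
2. **CRP.** Use the inclusion value as a covariate and only later days as outcomes, and list CRP as exploratory among the outcomes.
3. **Optional, basal dose only.** Because basal steps are percentages, analyse log basal dose with log starting dose and report a ratio with 95% CI. Exclude days on which basal insulin is paused, and report how many were excluded per arm. Keep prandial and correctional doses in units, since they can be zero and correctional insulin moves in units.

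The cost is one or two sentences and slightly more analysis work. Weight, height and date of birth are recorded, eGFR is among the inclusion blood samples, and the home dose is needed to apply Table 1 at all. With the log option, the basal result reads as a ratio instead of units.
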